### Mechanistic and other clinical outcomes

We will also assess additional outcomes that have proven to be established correlates and predictors of suicide ideation and behaviour:The *Beck Depression Inventory-II* (BDI-II; [4]) will be used to assess depressive symptoms. One of the most widely used measures of depression, this 21-item measure assesses the DSM diagnostic criteria for major depressive episodes. The BDI-II has consistently demonstrated good internal consistency and test–retest reliability amongst adult clinical outpatients [35] and inpatients [81].The *Beck Hopelessness Scale* (BHS; [2]) will provide a measure of negative future perceptions. Reliability estimates for the BHS have been reported as 0.88 across various clinical samples, including those with suicidal thoughts and behaviours and severe mental health problems [2].The *Defeat and Entrapment scales* developed by Gilbert and Allan [31] measure perceptions of being defeated and trapped, which have been established as key determinants of suicidal ideation and behaviour [86]. Cronbach’s alpha for the Defeat and Entrapment scales were reported as ranging from 0.93 to 0.86, respectively, suggesting high levels of internal consistency [31].

Other important clinical outcomes to be measured are distressing psychiatric symptoms, personality dysfunction, self-esteem and coping. These will be measured through the *Brief Symptom Inventory* (BSI; [22]), the *Standardised Assessment of Personality – Abbreviated Scale* (SAPAS; [62]), the *Robson Self Concept Questionnaire* (Robson, 1989) and the *Coping Inventory for Stressful Situations* (CISS; [27]). A global assessment of wellbeing come from completion of the *ICEpop CAPability measure for Adults* (ICECAP; [1]).

### Health economics measures:

Health status and quality adjusted life years (QALYs) will be measured using the 5-level version of the *EQ-5D* (EQ-5D-5L) and associated published utility tariffs recommended by NICE at the time of analysis [23, 42, 44]. The QALY will be used as the primary measure of health benefit for the economic evaluation. The EQ-5D is a validated generic health status measure, used in national health surveys in the United Kingdom and in clinical trials in mental health, covering five domains (mobility, self-care, usual activity, pain/distress, and anxiety/depression). The five level version will be used in this trial (no problems, slight problems, some problems, severe problems or unable to do activity). The QALY and the EQ-5D are the measures recommended for economic evaluations by NICE [65]. There are 3126 possible health states in the EQ-5D-5L (5 dimensions to the power of 5 levels = 55 = 3126). The health status profiles will be converted to utility values using the published utility tariffs for the EQ-5D-5. The QALYs will be estimated as:$$\mathrm{QALY}=\sum\left(({\mathrm U}_{\mathrm i}+\;{\mathrm U}_{\mathrm i+1}\right)\;/2\;\times\;\left({\mathrm t}_{\mathrm i+1}\;-\;{\mathrm t}_{\mathrm i}\right)$$

where U = utility value and t = number of days between assessments.

Data about the health and social care services used will be collected from an adapted version of the *Client Service Receipt Inventory* (CSRI; [5]) used in previous and ongoing trials in this population group. All contacts with health, social care, education and third sector organisations are recorded. This measure is designed to capture a broad range of services that participants engage with whilst in prison and following release from prison. For each contact, the table captures the name of service, whether the contact was in prison or the community, the number and duration of contacts, the nature of the contact (e.g. face-to-face, phone call) and who the contact was initiated by. There is good evidence that with support from the person administering the assessment, participants can complete the CSRI to provide valid self-report health service use data [11, 13, 49] with self-reporting shown to be as accurate, valid and reliable as case note review [11].

The cost of the PROSPECT programme will be derived from practitioner time attending initial training and ongoing supervision meetings, as well as a detailed log of therapy provided, completed by the Trial practitioners as part of the fidelity assessment. To maintain the blindness to allocation of research assessors, we will collect data on staff time costs, including training, preparation and clinical supervision, directly from the trial practitioners. The unit costs of NHS and social care services will be derived from national average unit cost data published in the NHS reference costs database, unit costs published by the Ministry of Justice and the annual Unit Costs of health and Social Care and the Unit Costs in Criminal Justice, both published by the Personal Social Services Research Unit (PSSRU). The costs of each service used by a participant will be estimated as the total use of a service multiplied by the unit cost of that service. These will be summed to generate a total cost for each participant.

The EQ-5D-5L and health service use data (CSRI) will be collected for all participants at baseline and 6-month assessments. Health economics data (on psychosocial support) will be collected in sealed envelopes (to maintain blindness) at each assessment and detailed process information about the PROSPECT programme will be collated from the practitioners’ files at the 6-month assessments after programme delivery has been completed. A healthcare reception screen should be conducted for all prisoners arriving at reception into prison custody. This screen is usually conducted by a prison nurse and so the consultation rate will be adjusted to provide a more accurate reflection of service use. The adjusted consultation rate will be calculated by reducing the total number of consultations by one for each new reception [54].

### Therapy process measure

For those randomised to the PROSPECT therapy programme arm of the trial, the therapeutic alliance will be assessed using the Working Alliance Inventory – short form (WAI; [39]), completed by both the participant and therapist, after approximately four sessions and again at the end of the therapy. To determine the effect of exposure to the intervention, the therapist will also record (i) the number of sessions attended, (ii) duration of each session attended, and (iii) perceived level of understanding and psychological formulation developed with the participant.

### Demographic, clinical and criminological data

In addition to the outcome measures detailed above, a range of demographic (age, gender, ethnicity), clinical (mental health diagnoses, previous suicide behaviour) and criminological (index offence, sentence length, previous imprisonments) details will also be collected at baseline. The researcher will also complete a contact sheet for each participant, which will include contact numbers and addresses provided by the participant, as well as a list of services they are likely to be in contact with post-release. This sheet will be completed in collaboration with the participant and the participant will sign the form to confirm they give the research team permission to contact them via the relevant services. Furthermore, clinical and prison records will be accessed, subject to participant consent, to collect relevant information that the participant is unable to self-report accurately, e.g. psychiatric diagnoses, offence details, serious incidents of self-injury and violence.

See Fig. 3 for further information on which time point each procedure or measure is completed.

**Fig. 3 Fig3:**
[figure not shown]
Outcome measures and time-points for collection

We recognise the importance of minimising respondent burden and have worked closely with our service user co-investigator and collaborators in the selection of the clinical outcome questionnaires. We believe that an acceptable assessment pack of outcome measures has been collaboratively developed which takes participant burden into account. We remain open to conducting further rationalisation of this assessment pack, and will prioritise this task within the initial work of the PROSPECT Service User Reference Group (SURG). Whilst a justification can be made for the inclusion of all of the outcome measures, we will continue to liaise with the SURG to reconsider the inclusion of each measure. We also envisage the SURG collaborating with us on the piloting of the administration of the self-report questionnaires to ensure data collection is appropriately conducted in a manner most acceptable to study participants.

### Data Management

#### Data collection tools and source document identification:

A web based electronic data capture (EDC) system will be designed, using the InferMed Macro 4 system. The EDC will be created in collaboration with the trial analyst/s and the CI and maintained by the King’s Clinical Trials Unit for the duration of the project. It will be hosted on a dedicated server within KCL.

The CI or delegate will request usernames and passwords from the KCTU. Database access will be strictly restricted through user-specific passwords to the authorised research team members. It is a legal requirement that passwords to the EDC are not shared, and that only those authorised to access the system are allowed to do so. If new staff members join the study, a user-specific username and password must be requested via the CI or delegate (e.g. Trial Manager) from the KCTU team and a request for access to be revoked must be requested when staff members leave the project. Study site staff experiencing issues with system access or functionality should contact the CI or delegate (e.g. Trial Manager) in the first instance.

Participant initials and date of birth will be entered on the EDC, NHS number, email addressed, participant names and addresses and full postcodes will not be entered into the EDC. No data will be entered onto the EDC system unless a participant has signed a consent form to participate in the trial. Source data will be entered by recruiting site staff, typically within 2 days of data collection by authorised staff onto the EDC by going to www.ctu.co.uk and clicking the link to access the MACRO 4 EDC system. A full audit trail of data entry and any subsequent changes to entered data will be automatically date and time stamped, alongside information about the user making the entry/changes within the system. The CI team will undertake appropriate reviews of the entered data, in consultation with the project analyst for the purpose of data cleaning and will request amendments as required. No data will be amended independently of the study site responsible for entering the data. At the end of the trial, the site PI will review all the data for each participant to verify that all the data are complete and correct. At this point, all data can be formally locked for analysis. Upon request, KCTU will provide a copy of the final exported dataset to the CI in.csv format and the CI will onward distribute as appropriate.

### Data storage and retaining study documentation:

All information will be kept strictly confidential and held in accordance with the principles of the Data Protection Act. Trial data will be stored safely and securely on a dedicated server at KCL. Any information about the participant obtained following their consent from their records held at site will be recorded against a participant identification number (pseudonymised format). Audio recordings of therapy sessions and qualitative interviews will be stored securely (indexed by study number only) on an encrypted and password-protected University of Manchester computer. Only the research team will have access to these data. Paper copies of the relevant trial documentation will be stored at the University of Manchester for a minimum of 15–20 years after publication of the trial results. For audit purposes, electronic copies will be retained for the duration advised by the NHS Research Ethics Committee (typically 5 years). We shall then deposit a pseudonymised data set in the databank maintained by the Offender Health Research Network.

### Data analyses of the RCT

Analysis will follow intention-to-treat principles and we will follow the CONSORT statement for non-pharmacological interventions. Treatment effects for patient-level outcomes will be analysed using a linear mixed models with random effects for practitioner and treatment allocation [76], fitted to the 6-month outcome variables.

Within the first six months of the trial, the trial statistician will develop a detailed statistical analysis plan for primary and secondary outcomes, including any sub-group analyses. This plan will be presented to and agreed with the IDMC and PSC prior to the allocation codes being released and commencement of any data analysis. The statistical analysis plan will be submitted for publication within the trial protocol as soon as is feasible and before the completion of data collection.

The following baseline data will be presented to demonstrate the extent of comparability between randomised groups: demographic (age, gender, ethnicity), clinical (mental health diagnoses) and criminological data (index offence, sentence length, previous imprisonments). A consort flow diagram will be used to show participant flow with reasons (where known) for discontinuation.

Primary analysis of suicide ideation (BSSI) measured at 6 months (window 5–9 months) will use a linear mixed model with adjustment for baseline BSSI, stratification criteria and prognostic baseline covariates. The adjusted mean differences will be presented with 95% confidence intervals. BSSI is expected to be positively skewed and so the standard error and confidence interval for the treatment effect will be estimated by applying a bootstrap procedure [25] using the percentiles based on the results of 5000 replications (using the trial participant as the sampling unit). Primary analysis of suicidal behaviours (SB) measured within 6 months from randomisation will use a mixed model for count outcomes. The appropriate model with be chosen depending on the distribution of this variable. Analysis will adjust for baseline BS, stratification criteria and prognostic baseline covariates. The adjusted incident rate ratio will be presented with 95% confidence intervals. Due to the hierarchical ordering of these primary outcomes, no confirmatory claims can be made with regards to treatment benefit on SB unless it has first been demonstrated on BSSI. Secondary outcomes will be assessed using linear mixed models with similar adjustments. Analysis of primary and secondary outcome measures will be by intention to treat and will therefore include outcomes for all randomised participants in the group to which they were allocated, regardless of protocol adherence.

A therapeutic dose response model will be used to assess the effect of time engaged in therapy on treatment benefit. A complier average causal effect (CACE) model will be used to examine the treatment effect in those defined as ‘compliers’. Compliance will be defined from practitioner notes as a participant having started the ‘CBSP Phase’ of therapy. Treatment effect will be estimated within the subgroups defined by whether a participant has a history of suicide (Yes/No). As the study was not powered to investigate subgroup effects, this will be a purely exploratory analysis. All inferential analyses will adjust for stratification factors used in randomisation. Additionally, baseline outcome and prognostic variables will be adjusted for to improve power. Where outcome variables are skewed, bootstrapped confidence intervals will be presented. There will be no interim analysis of outcome data during the trial.

All efforts will be made to obtain outcome data for randomised participants. This will include following up participants who transfer prisons or are released prior to their 6 month follow up assessment. Reasons for withdrawal of consent to follow up with be recorded and tabulated where participants are willing to provide a reason. The primary analysis will include all available data under a missing at random assumption. Sensitivity to missing data mechanisms will be assessed, and if required multiple imputation or inverse probability weighting used to account for missing outcomes.

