#### Sample size calculation

We use an approach based on a simple t-test for the between group comparison in the primary outcome which is specifically designed to account for differential clustering or partial nesting between the two arms. It is implemented in –clsampsi- in Stata. This approach requires the following assumptions:Effect size: We have powered our trial on the basis of clinical superiority compared to treatment as usual, and will conduct our analysis accordingly. We have powered to detect a standardised effect size of 0.36. This equates to an approximate mean difference of 3.9 in the primary outcome (Beck Scale for Suicide Ideation, BSSI) or 60% reduction in SB using estimates derived from our pilot RCT [74].Practitioner number: From our planned staffing of 4 practitioners at any one time, we have allowed for 7 practitioners to be used during the course of the whole trial (to account for practitioners leaving and being replaced). This also helps to improve the generalisability of the trial. We allow for a variance in the number of participants seen per practitioner (i.e. that this follows a Poisson distribution).Clustering: We account for differential clustering of 7 practitioners over trial duration in treatment plus TAU arm, average number of patients per practitioner of 18 and ICC = 0.01. No prior estimate of the ICC is available, but we consider this a conservative estimate to what is typically found in psychotherapy trials. We will include pre-specified prognostic variables for the outcome in our analysis models to further reduce the ICC. This approach is robust to observed increases in ICC as the number of practitioners (clusters) increases. For the calculation, we consider the control arm as clusters of size 1 with ICC = 0.Power: We assume a conservative baseline-endpoint correlation of 0.6 (0.6 in pilot, 95% CI 0.4–0.7), a two-sided significance level of 0.05 and statistical power of 90% with equal allocation to two arms. Given these assumptions, an analysis set of 250 (125 per group) has 80% power to detect an effect size of 0.36. Power will be increased by inclusion of baseline covariates where possible.Attrition: Although attrition rates for prison-based trials can be over 50% (e.g. [8, 70]), our pilot trial was sufficiently resourced to enable research staff to maintain regular contact with participants, resulting in an attrition rate of 30%.

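### The primary BSSI interval comes from a bootstrap of individual participants, which leaves out practitioner variance; if the practitioner ICC is above 0, the interval is too narrow

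*Protocol article*

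**What the plan says.** Three statements in the protocol article bear on this.

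- **Sample size calculation.** "We account for differential clustering of 7 practitioners over trial duration in treatment plus TAU arm", with an average of 18 patients per practitioner and ICC 0.01. Caseloads vary: "We allow for a variance in the number of participants seen per practitioner (i.e. that this follows a Poisson distribution". The control arm is treated as unclustered. The section concedes that no earlier estimate of the ICC exists, but regards 0.01 as conservative.
- **Data analyses of the RCT, general model.** Patient-level outcomes are to be "analysed using a linear mixed models with random effects for practitioner and treatment allocation".
- **Data analyses of the RCT, primary BSSI analysis.** Because BSSI is expected to be skewed, the standard error and confidence interval of the treatment effect are taken from a bootstrap, using "the percentiles based on the results of 5000 replications (using the trial participant as the sampling unit". Resampling or regeneration of practitioners is not mentioned.

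The same section says that no confirmatory claim on suicidal behaviour can be made unless benefit is first shown on BSSI. For other skewed outcomes it promises bootstrapped intervals without naming a sampling unit.

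**The concern.** The design and the model treat the practitioner as a source of variance in the therapy arm; the reported interval does not. A percentile interval shows how the estimate moves when the resampled units are redrawn. If those units are participants, the practitioners and their particular effects stay fixed across replicates, so the interval answers a question about these practitioners only. That sits badly with a model that takes practitioner as random, and with the sample size section's remark that using several practitioners helps generalisability.

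BSSI is the first-ranked outcome and the gate to suicidal behaviour. An interval that is too narrow on BSSI raises the chance of a false claim there and lets the second outcome be tested too often.

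**Working it through.** **Inputs (Sample size calculation).** Two-sided alpha 0.05; "We have powered to detect a standardised effect size of 0.36"; "This equates to an approximate mean difference of 3.9 in the primary outcome", so the implied SD is 3.9/0.36 = 10.8 points; "7 practitioners over trial duration in treatment plus TAU arm, average number of patients per practitioner of 18 and ICC = 0.01"; Poisson caseloads; control ICC 0; baseline-endpoint correlation 0.6; 125 analysed per arm.

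**Reproducing the stated figures.**
- No clustering, no correlation: SE = √(2/125) = 0.1265, power 0.81.
- Design effect 1 + 17 × 0.01 = 1.17 in the therapy arm, no correlation: SE = √(2.17/125) = 0.1318, power 0.78.
- Correlation 0.6 added: SE = √(0.64 × 2.17/125) = 0.1054, power 0.93 with a normal reference and 0.81 with a t reference on 6 df.
- Attrition: 250/0.7 = 358, against 360 planned.

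The stated 80% is therefore reachable under some variants. The section also gives "a two-sided significance level of 0.05 and statistical power of 90% with equal allocation to two arms" for the same assumptions; that inconsistency is separate from this point.

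**Analytic size of the error.** Let r be the true SE divided by the SE that omits practitioner variance. With equal arms r = √((DE + 1)/2), and type I error = 2 × (1 − Φ(1.96/r)). Poisson caseloads (squared coefficient of variation 1/18) change the multiplier from 17 to 18(1 + 1/18) − 1 = 18. If baseline adjustment removes residual variance but no practitioner variance, the ICC becomes ICC/0.64.

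| ICC | Practitioner share | DE | r | Type I error |
|---|---|---|---|---|
| 0 | none | 1.00 | 1.000 | 5.0% |
| 0.01 | as stated | 1.18 | 1.044 | 6.0% |
| 0.01 | 0.01/0.64 = 0.0156 | 1.28 | 1.068 | 6.7% |
| 0.05 (assumed) | as stated | 1.90 | 1.204 | 10.4% |
| 0.05 (assumed) | 0.05/0.64 = 0.078 | 2.41 | 1.305 | 13.3% |

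Equal caseloads of 18 (DE 1.17 at ICC 0.01, 1.85 at ICC 0.05) give 6.0% and 10.1%.

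**Simulation.** Null trials with 7 practitioners, Poisson(18) caseloads, 125 controls, correlation 0.6, four sites in the model and a normal outcome. The practitioner random-effect model was refitted in every participant-level resample and percentile limits were taken.
- ICC 0 (4,000 trials, 1,000 resamples): 5.2%.
- ICC 0.01 (same settings): 7.2%, Monte Carlo SE 0.4 points. Mean bootstrap SE 0.1015 against an actual SD of 0.109, a ratio of 0.93. Without the random effect the error was also 7.2%.
- ICC 0.05 (2,500 trials, 300 resamples): 14.6%; SE 0.100 against 0.132.
- With only 300 resamples and 2,500 trials the rates at ICC 0 and 0.01 were 6.5% and 8.0%. Part of the excess in the shorter runs, including the 14.6%, may therefore come from the small number of resamples.
- A second simulation gave 4.9% at ICC 0, about 6-8% at 0.01 and about 14% at 0.05.

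In BSSI points at ICC 0.01, the bootstrap SE is 0.1015 × 10.8 = 1.10 and the correct one 0.109 × 10.8 = 1.18. The half-widths are 2.15 and 2.31, so the planned interval is about 7% too narrow.

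**What a valid interval costs.** Approximate Satterthwaite df = 2.17² / (1.17²/6 + 1/124) = 4.709/0.236 ≈ 20, so t = 2.09 and 2.09/1.96 = 1.065. Multiplied by an SE ratio of 1.042 to 1.068, the interval is 11-14% wider. Power at effect 0.36 (noncentrality 0.36/0.1054 = 3.42) is about 0.90 on 20 df and 0.81 on 6 df.

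**The case against.** - **The mixed model already carries a practitioner random effect, and site is adjusted for.** True of the point estimate, but neither repairs the interval. Refitting the model in each resample changed almost nothing. Practitioner variance exists only in the therapy arm, so a site effect shared by both arms cannot absorb it.
- **The excess depends on the ICC.** This stands. At ICC 0 there is none, and the protocol calls 0.01 conservative. If therapy did nothing through any practitioner, therapy-arm practitioner variance should be near zero. The inflation belongs to the null of no average effect with practitioners who differ. When therapy works and practitioners differ, the loss shows as coverage below 95%. Against this, the protocol has no ICC estimate, and the planned interval would not widen if the ICC proved larger.
- **The larger figures use an ICC five times the stated one.** This also stands: 0.05 is an assumption that shows the range.
- **No test or decision rule for BSSI is spelled out.** Correct. That the bootstrap interval decides the outcome is an inference, though a reasonable one, since it is the only inferential output named for BSSI.
- **Treatment as a random effect.** A reader might infer from "analysed using a linear mixed models with random effects for practitioner and treatment allocation" that treatment is itself random, so that no fixed difference is estimated. The text does not support this. The phrase can mean a treatment coefficient varying by practitioner, and the same section promises adjusted mean differences with confidence intervals. It is loose wording at most.

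**Conclusion.** The point holds conditionally. As written, the standard error and interval for BSSI leave out a variance component that the design and the model both recognise. At ICC 0.01 the standard error is about 4-8% too small and two-sided type I error is about 6-8%. At an assumed ICC of 0.05 the error is about 10-15%, and at ICC 0 it is nominal. These figures rest on 7 practitioners with about 18 participants each, 125 analysed per arm, and a normal outcome in the simulations.

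It would be too strong to say that type I error exceeds 5% whatever the ICC, or that the plan ignores clustering altogether. Because the excess is modest at the only ICC the document gives, this is something that should be fixed rather than a fatal fault. It still merits action because the sampling unit is stated outright and BSSI gates the claim on suicidal behaviour.

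**What to change.** Take the primary BSSI standard error and confidence interval from the partially nested mixed model: fixed treatment effect, practitioner random effect in the therapy arm only, and Satterthwaite or Kenward-Roger degrees of freedom. The small-sample correction matters. In simulation a normal reference gave 5.3-5.8% at ICC 0.01 and 8.0% at 0.05, while a Satterthwaite-type interval held the error at 4.7% and 5.5%.

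If a bootstrap is kept for skewness, use one that regenerates practitioner effects in the therapy arm. Simply resampling 7 practitioners was not tested and should not be assumed adequate. Keep the participant-level bootstrap only as a labelled sensitivity analysis. State the sampling unit for the other skewed outcomes, and reword the model sentence so that treatment is plainly fixed.

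The cost is analysis wording and code, with no new data. The interval is roughly 11-14% wider at ICC 0.01. Power at 250 analysed and correlation 0.6 falls from 0.93 (normal reference) to about 0.90 on 20 df, and to 0.81 even on 6 df.
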